## Data Analyses

Data cleaning will be on-going throughout data collection. Initial data analyses of youth enrolled in the first 9 months of the RCT will be completed in months 15-20. Detailed analysis syntax and modeling will be retained for use in the final modeling/analyses when data collection is complete. Statistical significance will be set at p<0.05 for all analyses.

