# Statistical Plan

## Sample Size Determination

The size of the study sample will be determined by the number of eligible youth contacts (with 1Call1Click or directly to the research team). Our pilot study approached 5-10 youth/week via 1Call1Click with 25% enrolling, providing an expected 400-800 potential and ~100-200 enrolled participants over 18 recruitment months. Complete data for 122 youth would provide 80% power to detect a 3.4 point difference in emotional health (Strengths & Difficulties Questionnaire), equivalent to the 19.5% improvement observed in our 3-month pilot study.

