# Dissemination \ Publication Plan

Our equity diverse, Lived Experience Advisory Group (LEAG) is comprised of 10 youth and 5 parents, all of whom have lived experience of youth mental distress. The LEAG developed our KT plan and will continue to guide our KT materials/activities. The KT plan they developed includes Annual Grand Rounds presentations (Y1: study protocol, Y2: efficacy RCT data, Y3: healthcare system data) because youth tell us that informed clinicians are the most effective avenue for sharing study information. Youth-written project summaries, infographics and videos will be developed and distributed to all youth partner organizations and networks/sites. Our LEAG members will also distribute the study results via social media networks. Each youth will receive their own assessment outcomes and have access to study presentations/results via the Healthier CHEO Kids web site ([www.cheori.org](http://www.cheori.org)) and partner networks. We will also invite study participants to contribute to the KT materials/activities as we found this approach very effective during our pilot study of the HELP e-resources.

Healthcare system results will be disseminated to professionals, families, hospital administrators and policy makers via a Children’s Healthcare Canada webinar presentation. Academic presentations will target paediatricians (Canadian Paediatric Society conference presentation) and exercise medicine professionals (North American Society for Pediatric Exercise Medicine conference presentation). We will publish three papers from this study in peer-reviewed journals for optimal dissemination of our research to the academic community. In year 1, we will publish the study protocol. In year 3, we will publish two papers reporting the study results. One paper will focus on the therapeutic impact of the intervention. The second paper will focus on the impact of this new model of care for the healthcare system. All papers will be published in open access journals.

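### The months 15-20 initial analysis is not declared masked or non-inferential; if it is a by-arm look that can support an efficacy claim, overall type I error is about 8.3%, not 5%

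*Protocol*

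**What the plan says.** The Data Analyses section of the protocol first says that data cleaning is continuous. It then adds: "Initial data analyses of youth enrolled in the first 9 months of the RCT will be completed in months 15-20". The next sentence ties this work to the end of the trial: "Detailed analysis syntax and modeling will be retained for use in the final modeling/analyses when data collection is complete". The paragraph closes with one threshold: "Statistical significance will be set at p<0.05 for all analyses". The initial analysis is not exempted.

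Sample Size Determination expects "100-200 enrolled participants over 18 recruitment months" and leaves the final number open: "The size of the study sample will be determined by the number of eligible youth contacts". The only powered figure is this: "Complete data for 122 youth would provide 80% power to detect a 3.4 point difference in emotional health".

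Study Design places efficacy assessments at 0, 3, 6 and 12 months. Efficacy Outcomes defines the primary outcome as the change in SDQ from baseline to 6 months, analysed in a repeated measures model with five named covariates. It later repeats those covariates for all models.

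The Dissemination \\ Publication Plan lists "Annual Grand Rounds presentations (Y1: study protocol, Y2: efficacy RCT data, Y3: healthcare system data" and places the two results papers in Year 3.

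The protocol does not say whether the initial analysis is pooled, masked or by arm. It has no stopping rule and no rule for an early claim of success.

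**The concern.** Taken together, these statements look like an efficacy look while the trial is running. The window for the initial analysis opens when the first-9-month cohort has completed the primary endpoint. The models are carried forward, the 5% threshold covers every analysis, and efficacy data are to be presented in Year 2.

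Two things are at stake. The first is the error rate: if the same youth are tested by arm once early and again at the end, each time at 0.05, and either result can be put forward as showing efficacy, the chance of a false claim exceeds 5%. The second is bias: the SDQ is completed by youth who know whether they have access to HELP. By-arm results presented before the assessments are complete could shift the expectations and answers of those still reporting. A blinded assessor, which the protocol provides, does not prevent that.

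**Working it through.** **1. The plan's own figure.** The 122 complete cases cannot be reproduced independently because no SD is given. It can be back-solved, assuming equal arms of 61, two-sided 0.05 and 80% power:

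SD = 3.4 / [(1.960 + 0.842) × √(2/61)] = 3.4 / 0.507 = 6.70 SDQ points.

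This SD is used only in step 3.

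**2. Calendar, counted from the start of recruitment.**

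- Youth enrolled by month 9 reach 6 months by month 9 + 6 = 15, when the initial analysis window opens.
- Last 6-month assessment: 18 + 6 = month 24.
- Last 12-month assessment: 18 + 12 = month 30.
- Year 2 ends at month 24 if years count from the start of the trial.
- Share of the sample in the initial analysis, with even accrual: 9/18 = 0.5, or about 50 to 100 of the expected 100 to 200 youth (61 of 122 complete cases).

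**3. Error rate if either look can support a claim.** Let t be the information fraction at the first look. Under no effect, the two test statistics are bivariate normal with correlation √t. At t = 0.5 the correlation is 0.707. The overall error is 1 − P(|Z1| < 1.96 and |Z2| < 1.96).

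| Information at first look | Overall two-sided type I error |
|---|---|
| 0.3 | 8.9% |
| 0.4 | 8.6% |
| 0.5 | 8.3% |
| 0.6 | 8.0% |
| 0.7 | 7.6% |

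The result depends little on the even-accrual assumption. With the back-solved SD, power for 3.4 points at the first look is Φ(3.4 / [6.70 × √(2/30.5)] − 1.960) = Φ(0.02), about 51%. So if the assumed effect is real, the early look has about an even chance of reaching p<0.05.

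**4. Error rate if only the final test counts.** With one model fixed beforehand, the final test on all data at 0.05 has a 5.0% error rate, whatever was seen earlier.

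If the first half were used to pick the most favourable of 2 to 5 candidate models, the final test alone would run at about 6.3% to 12.7%. This comes from simulation, with an assumed correlation of 0.5 to 0.9 between models. It is only an illustration; the protocol describes no such search.

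**5. Thresholds that would hold about 5% at t = 0.5.**

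- p<0.001 at the first look and 0.05 at the final: 5.02% overall.
- O'Brien-Fleming: 0.0052 at the first look and 0.0480 at the final: 5% overall.

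**6. Who is still reporting when results could appear.** With even accrual, the share of the sample whose 6-month SDQ is outstanding at month m is (24 − m)/18. That is 9/18 = 50% at month 15 and 4/18 = 22% at month 20. For the 12-month assessment the share is (30 − m)/18, which is 10/18 = 56% at month 20.

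**The case against.** The Data Analyses section does not name the SDQ, a comparison by arm or any unmasking. It can be read as a rehearsal of the code next to a sentence on data cleaning. That stands: the by-arm test is an inference from the timing, the reuse of the models and the Year 2 item.

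A reader might go further and infer that the 5% level is already lost. The documents do not support that. They contain no early-success rule, the results papers are placed in Year 3, and a final test with a fixed model keeps its 5%.

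A reader might also infer that the final model will be chosen on the early data. Efficacy Outcomes argues against this, because the outcome, the 0 to 6 month window, the model type and the covariates are already set. What remains open, such as the covariance structure, is commonly settled in a SAP.

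The link to the Year 2 presentation is likewise inferred. The plan does not say which analysis feeds it or when Year 1 begins. The effect on referrals is narrow: recruitment ends at month 18, so a talk based on work from months 15-20 could influence referrals only between about months 15 and 18. Clinician referral is also a secondary recruitment route.

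Finally, masking and alpha for an early look could be set in a SAP. That answers less than it seems to. The protocol states one threshold for all analyses, and a SAP would have to override that sentence.

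**Conclusion.** The point holds in conditional form and should be fixed. The protocol schedules an analysis for when about half the primary outcome is complete, carries its modelling into the final analysis, does not exempt it from the general 5% threshold, and plans an efficacy presentation before, or just as, the last 6-month assessment falls due.

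If that analysis is by arm and either look can support an efficacy claim, overall two-sided type I error is about 8.3% (7.6% to 8.9% for information fractions from 0.7 down to 0.3). If the model is locked first and only the final test is confirmatory, 5% holds. The protocol does not say which applies.

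The figure assumes two-sided tests and even accrual. The risk of biased self-report from an early release is real but cannot be sized from the documents. It would concern the 22% to 50% of youth still awaiting the 6-month SDQ at months 15-20, and more at 12 months.

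**What to change.** In Data Analyses, state three things:

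- The months 15-20 work is limited to data cleaning and testing of syntax on pooled data or scrambled arm codes.
- The primary model is locked before any arm-coded outcome is seen.
- The 0.05 threshold applies once, for confirmatory purposes, to the final primary test.

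If an arm-coded look is wanted, state that and test it at p<0.001 with 0.05 at the end (about 5.02% overall), or use the O'Brien-Fleming split of 0.0052 and 0.0480. The split should be recalculated if the information fraction is not close to one half.

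In the Dissemination \\ Publication Plan, hold the efficacy presentation until the last 6-month assessment is complete and locked, which is after about month 24.

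The cost is a few sentences and an efficacy talk that moves from Year 2 to Year 3. No extra participants or assessments are needed. The change has to be made before the initial analysis, because arm-coded results cannot be unseen.

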### Efficacy Outcomes

The primary outcome is youth emotional well-being as measured by the Strengths & Difficulties Questionnaire (SDQ^34^). We define a clinically significant improvement as a score decrease of 15%, with the reduction occurring only when participants have engaged with the intervention. This change is just less than 1/2 of the SDQ improvement observed after 6 months of specialist community mental health services^43^. We do not expect HELP benefits to be equivalent to traditional mental health interventions. However, we believe that the ability to improve emotional health half as well as traditional therapies would provide a meaningful and important change. In our pilot study, SDQ scores improved by 19.5% in 3 months among engaged youth. We will evaluate the change in SDQ from baseline to 6 months in a repeated measures model adjusted for age (years), gender, intervention adherence, type of mental health concern (e.g., anxiety, depression, etc. as documented during 1Call1Click intake), and support referral (community or specialist services recommended by 1Call1Click intake staff). The impact of sex will be investigated if participants include a sufficient number of youth who do not identify as the gender aligned with their sex.

Secondary efficacy outcomes are measures of readiness for behaviour change (i.e., stage of change) and sleep, physical activity and screen time behaviour. Behaviour change theory emphasizes that individuals move through a series of stages, with the most effective intervention differing for each stage. HELP supports youth in all stages of change. “Learn” targets youth not yet considering behaviour change. “Pro’s and Con’s” guides youth to address their ambivalence towards change. “Goals” provide step-by-step plans so youth can act on their intention to change behaviour. “Roadblocks” support the maintenance of recent behaviour changes. Paired t-tests will examine participants’ stage of change at enrollment and 6 months to assess whether HELP enhanced their readiness for behaviour change. Modeling how the behaviour change stage differs, with adjustments for age, gender, intervention adherence, type of mental health concern and support referral, will assess whether HELP similarly impacts behaviour change among all youth. The same analyses will be completed for each behaviour outcome with stage of change at 6-months a mandatory variable as theory indicates that achieving Stages 3 to 5 is required for behaviour change to occur (Stages 1 & 2 are moving toward the decision to change behaviour).

A repeated measures model of the primary and secondary outcomes will evaluate changes between study groups, comparing changes occurring during intervention access to changes when the intervention is not available. Changes between the 0 and 6-month assessments for youth randomized to immediate intervention access and between the 6 and 12-month assessments for youth randomized to the wait list group will evaluate HELP e-intervention efficacy. Differences between the 6 and 12-month assessments for youth randomized to immediate intervention access will evaluate the sustainability of the intervention effects. Differences between the 0 and 6-month assessments for youth randomized to the wait list group will evaluate changes in study outcomes over time without the HELP e-intervention. Comparisons between 0 and 3-month and 3 and 6-month outcomes will determine the required length of the HELP e-intervention for optimal outcomes. All models will be adjusted for age, gender, intervention adherence, type of mental health concern and support referral.

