# Study Design

This research will investigate the patient and healthcare system impacts of the HEalthy Lifestyle Project (HELP) e-intervention. The research design is a randomized, controlled trial comparing youth who immediately receive the intervention to youth randomized to receive the intervention 6-months later (wait list control). Efficacy outcomes will be assessed at 0, 3, 6 and 12 months. Healthcare system impacts will be extracted from medical records from 0 to 18 months.

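### The protocol's adjustment list omits the baseline value of the outcome and states no common baseline mean, so the 0-to-6-month comparison, read as written, may give up precision at no benefit

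*Protocol*

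**What the plan says.** The protocol's Efficacy Outcomes section sets out the primary analysis: "We will evaluate the change in SDQ from baseline to 6 months in a repeated measures model adjusted for age (years), gender, intervention adherence", with type of mental health concern and support referral completing the list. Later in that section, after describing a repeated measures model that compares changes between study groups, it says "All models will be adjusted for age, gender, intervention adherence, type of mental health concern and support referral". For the behaviour outcomes it also makes stage of change at 6 months mandatory.

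The baseline value of the outcome is in neither list, although Study Design and Study Assessments have every participant complete the questionnaires at month 0. The protocol does not say whether the month-0 score is a response in the model, whether the response is a change score, or whether the arms are held to one baseline mean.

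Sample Size Determination says "Complete data for 122 youth would provide 80% power to detect a 3.4 point difference in emotional health". It gives no SD, no correlation between visits and no allocation ratio. Data Analyses sets the level: "Statistical significance will be set at p<0.05 for all analyses", without saying whether tests are one- or two-sided.

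**The concern.** In a randomised trial with a continuous outcome measured at baseline and follow-up, the baseline score is usually one of the strongest predictors of the follow-up score. An analysis that only subtracts it fixes its coefficient at 1. An analysis that conditions on it lets the data choose the coefficient, and in large samples its variance is never larger.

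Calling the analysis a repeated measures model does not settle the matter. If each arm has its own free baseline mean, the group-by-time contrast is a difference of changes and has change-score variance. The efficient result needs baseline as a covariate, or as a response with a common mean across arms. The protocol states neither, and an analyst who followed its covariate list literally would use neither.

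This matters more here because precision is limited. The 122 is a count of participants with complete data, while recruitment is described as "providing an expected 400-800 potential and ~100-200 enrolled participants over 18 recruitment months", so the target may not be reached. The 3.4-point difference is described as "equivalent to the 19.5% improvement observed in our 3-month pilot study", which is larger than the change the protocol calls clinically significant: "We define a clinically significant improvement as a score decrease of 15" per cent.

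**Working it through.** **Inputs from the protocol.** 122 participants with complete data, 80% power, a 3.4-point difference, significance at 0.05, 3.4 points equated with 19.5%, and a 15% threshold.

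**Assumptions, because the protocol gives no figure.** 1:1 allocation (61 per arm); two-sided test; equal SD at both visits; baseline-to-6-month correlation r from 0.3 to 0.9; no other covariates in the power calculation.

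**1. The plan's own figure.** With no SD stated, 122 cannot be reproduced independently; it can only be solved backwards. For a two-sample t-test with 61 per arm, 80% power needs a standardised difference of 0.511, so SD = 3.4 / 0.511 = 6.65. The normal approximation gives 6.70, and with 6.70 the usual formula returns 61 per arm, 122 in all. The statement is therefore coherent, but it does not show whether this SD belongs to a change or to a single score.

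**2. Variance of the arm contrast**, with s the SD of one score and n = 61 per arm:

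- Change score, or repeated measures with free baseline means: (2/n) × 2(1−r) × s²
- Baseline as covariate, or common baseline mean: (2/n) × (1−r²) × s²
- Ratio, second to first: (1−r²) / [2(1−r)] = (1+r)/2

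At r = 0.6, generalised least squares gives 0.0262 s² for the free-baseline model, the same as the change score, and 0.0210 s² for the common-baseline model, the same as ANCOVA: 20% less. Adding the 3-month visit under compound symmetry alters neither figure.

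**3. If 6.65 is the SD of change.** Residual SD after adjustment is 6.65 × √((1+r)/2); unadjusted power at 3.4 points is 80%.

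| r | variance ratio | residual SD | power at 3.4 |
|---|---|---|---|
| 0.3 | 0.65 | 5.36 | 94% |
| 0.5 | 0.75 | 5.76 | 90% |
| 0.7 | 0.85 | 6.13 | 86% |
| 0.9 | 0.95 | 6.48 | 82% |

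The 15% threshold is about 2.6 points: 3.4 / 0.195 = 17.4, and 0.15 × 17.4 = 2.6. Read as an arm difference, it has 58% power unadjusted, rising to 70% at r = 0.5 or 65% at r = 0.7.

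**4. If 6.65 is the SD of a single score.** The SD of change is 6.65 × √(2(1−r)) and the adjusted SD is 6.65 × √(1−r²).

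| r | power at 3.4, change score | power at 3.4, baseline-adjusted |
|---|---|---|
| 0.3 | 66% | 84% |
| 0.5 | 80% | 90% |
| 0.7 | 95% | 97.5% |

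The gain is large at low correlation and slight at high correlation.

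**The case against.** The strongest reply is that the protocol names a repeated measures model over the assessment times, so the month-0 score may well be one of the responses. If the arms share a baseline mean in that model, the variance equals that of ANCOVA and nothing is lost. The exact form could properly be left to a statistical analysis plan. This stands as a limit: the loss may be zero. It does not remove the point, because the protocol fixes the covariate set twice without baseline and describes a comparison of changes, which points to the less efficient form.

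A reader might go further and infer that the list is complete and so rules baseline out. The documents do not support that. The primary-model sentence also leaves out study group, visit and their interaction, so it is not a full model specification.

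A reader might also infer that the result would be biased by baseline imbalance or regression to the mean. Under randomisation the change-score contrast is unbiased, and chance imbalance is already counted in its variance. It is not a harm on top of lost precision.

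Nor can one power gain be attributed to this plan. The calculations leave out the listed covariates, including intervention adherence, which is measured after randomisation and closely tied to arm, since controls have no access from 0 to 6 months. Adjusting for adherence is a separate and more serious problem, but removing it would still leave baseline out.

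**Conclusion.** The point holds as one of precision, conditional on the model form. The stated covariates omit the baseline outcome and no common baseline mean is stated. Under the literal reading, the randomised 0-to-6-month contrast has 1/0.95 to 1/0.65 times the variance it need have, that is about 1.05 to 1.54 times, for assumed r of 0.9 to 0.3. What this means for power depends on an SD and a correlation that the protocol does not give: on the change-SD reading, 2 to 14 percentage points at 3.4 points; on the single-score reading, about 18 points at r = 0.3 but only about 2.5 at r = 0.7. These figures assume 1:1 allocation, a two-sided test, equal SD at both visits and no other covariates.

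It is tempting to extend the point to every secondary comparison. That goes too far: the wait-list comparison from 6 to 12 months starts from the 6-month score, so a month-0 covariate does not address it.

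**What to change.** State in Efficacy Outcomes that the primary model takes SDQ at 3 and 6 months as responses, with arm, visit and arm-by-visit terms and baseline SDQ as a covariate. Alternatively, include month 0 as a response with the arms constrained equal at baseline. Name the arm difference at 6 months as the primary contrast. Do the same, with its own baseline value, for the randomised 0-to-6-month comparison of each secondary outcome. If a common-baseline model is already intended, saying so is enough. The wait-list 6-to-12-month comparison needs its own specification.

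In Sample Size Determination, add the SD used, whether it is that of a score or of a change, and the assumed correlation, so that the 122 can be tied to the model.

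The cost is a few lines of text and one degree of freedom in the model. No new data are needed, since baseline questionnaires are already planned for everyone.

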## Study Objectives

This study will evaluate the efficacy of 6 months of HELP e-intervention access with kinesiologist support in a randomized controlled trial to determine if the changes in emotional health (primary outcome) and lifestyle behaviours (secondary outcomes) differ from changes among youth with delayed intervention access (control condition). Sustainability of the intervention will be assessed for an additional 6 months. Participants will be youth 12-17 years of age who contact youth mental health services (1Call1Click). We will also evaluate the impact of the HELP e-intervention on the use of mental healthcare services, the need for mental health professional support of lifestyle behaviours and the association between self-reported and objectively measured lifestyle behaviours.

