## Expected Duration of Participation

Youth will participate in the study for 12 months. All study visits and assessments are completed remotely. Youth can choose to complete the assessments via RedCAP survey or to have paper copies of the questionnaires sent by mail. The research coordinator will work virtually with each participant to support questionnaire completion. Completion of all questionnaires will require approximately 1 hour at each assessment timepoint. One of every three participants will be randomly selected to complete the objective behaviour measurements in addition to the questionnaires. Accelerometers will be distributed and collected by mail so that in-person visits to CHEO are not required. Participants selected for the objective measures will be required to wear an accelerometer on an elastic waistband 24 hours per day for 7 consecutive days. They will also be required to submit a screen shot of their social media screen time (app that already exists in smartphones) daily for the same 7 days. After the four assessment timepoints have been completed, youth will no longer be required to perform study activities but data collection on healthcare system impacts will continue to be collected via medical chart review for an additional 6 months. Participants randomized to the wait list control group will have access to the HELP e-intervention between the 6 and 12-month assessment timepoints.

| **Study Group** | **0 mos** | **0 to 3 mos** | **3 mos** | **3 to 6 mos** | **6 mos** | **6 to 12 mos** | **12 mos** | **12 to 18 mos** |
| --- | --- | --- | --- | --- | --- | --- | --- | --- |
| Intervention | Assess | HELP | Assess | HELP | Assess | ----- | Assess | Medical chart |
| Wait List Control | Assess | ----- | Assess | ----- | Assess | HELP | Assess | Medical chart |

Assess = completion of study questionnaires and objective measures (if applicable)
HELP = access to the HELP e-intervention with kinesiologist support
Medical chart = evaluation of mental health service use and inclusion of lifestyle behaviours in mental health service supports via medical chart review for 18 months from study enrollment

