### HELP E-Intervention

All study participants will have access to the HELP e-intervention either immediately (HELP access between 0 and 6 months) or after a wait of 6 months (control condition, access between 6 and 12 months). The use of a wait list control is expected to decrease the impact of randomization on study recruitment and retention. Our unique HELP e-resources utilize age-appropriate graphics and interactive formats developed collaboratively with youth/parent/clinician partners. There are 4 sections: 1) Know Your Habits, 2) Physical Activity, 3) Screen Time, 4) Sleep. Know Your Habits provides youth with their personal baseline questionnaire results. Messages are tailored to each youth’s readiness for behaviour change and assessment results. Each behaviour section (physical activity, screen time, sleep) has 4 sub-sections. “Learn” conveys information linking the behaviour and youth mental health and targets youth not yet contemplating behaviour change. “Pros and Cons” targets ambivalence, supporting youth to consider the barriers/facilitators of behaviour change. “Goals” guides youth to choose from >70 step-by-step change plans. Each plan contains a sequence of 6-8 steps that youth complete to achieve their goal. Steps vary in required time (2-30 mins) and youth proceed through the steps at their preferred pace. SMART goal, overcoming road blocks and additional kinesiologist support resources are also provided. Youth can track their goals and accomplishments on the website. Access to all HELP e-modules is available to all youth but the website suggests individualized avenues for change based on each participant’s assessment results. Sample pages from the HELP e-intervention are provided in Appendix H.

Each participant will have a unique login to the HELP e-intervention (found at www.cheoactive.ca). By automatically tracking e-resource use (site visits, interactivity use, knowledge component completion), the website provides data regarding participant engagement with the intervention. These data also assess the frequency or type of e-resource use, important considerations in analyzing the intervention impact on behaviour change. Comparing initial and post-intervention questionnaire responses will indicate the potential emotional health/lifestyle behaviour change impacts of HELP e-resource access.

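### Intervention adherence, which arises after randomisation and which wait-list youth cannot have before month 6, should not adjust the primary between-arm SDQ comparison

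*Protocol*

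**What the plan says.** The trial's stated purpose is a randomised contrast: "to determine if the changes in emotional health (primary outcome) and lifestyle behaviours (secondary outcomes) differ from changes among youth with delayed intervention access" (Protocol, Study Objectives). Under Efficacy Outcomes the primary analysis is introduced with "We will evaluate the change in SDQ from baseline to 6 months", and the model is specified as "in a repeated measures model adjusted for age (years), gender, intervention adherence, type of mental health concern" and support referral. The same section states that "A repeated measures model of the primary and secondary outcomes will evaluate changes between study groups", and closes with "All models will be adjusted for age, gender, intervention adherence, type of mental health concern and support referral". No efficacy model without adherence is described, and adherence is not set apart as a per-protocol, dose-response or causal analysis.

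Two other sections show what adherence can be in each arm. Under HELP E-Intervention: "By automatically tracking e-resource use (site visits, interactivity use, knowledge component completion), the website provides data regarding participant engagement with the intervention". Under Expected Duration of Participation: "Participants randomized to the wait list control group will have access to the HELP e-intervention between the 6 and 12-month assessment timepoints".

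**The concern.** The other adjusters (age, gender, type of concern, support referral) describe the youth at entry. Adherence does not. It comes into being after allocation, it is chosen by the participant, and in the primary window only one arm can have any. The protocol itself reports that starting routine engagement was a struggle for most pilot participants, so use will vary, and it may well track motivation or prognosis.

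If such a variable adjusts the change in SDQ, the arm coefficient is read at a common value of adherence. The only value the two arms share over months 0 to 6 is zero. The arm effect then compares a HELP youth who used nothing with a control, and any benefit that comes through use moves to a coefficient that randomisation does not protect. An effective programme could look null, and an inert one could look harmful or helpful depending on who engages.

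**Working it through.** **1. Inputs.** From Sample Size Determination: 122 youth with complete data, 80% power, a 3.4-point difference. From Data Analyses: significance at 0.05. Two-sided testing and 1:1 allocation (61 per arm) are my assumptions. No SD is given, so the 122 cannot be reproduced independently, only solved backwards:

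SD = 3.4 / [(1.960 + 0.842) × √(2/61)] = 3.4 / (2.802 × 0.1811) = 6.70 by the normal approximation, or 6.65 by the t-test. An SD of 6 would need 98 youth, 7 would need 134 and 8 would need 174. The argument does not depend on this value.

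**2. Assumed adherence.** Zero in controls. In the HELP arm, uniform over 0 to 1: mean 0.5, variance 1/12. Lower SDQ is better, so benefit is negative.

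**3. What the adjusted arm coefficient is.** Regress change on arm and adherence. The arm coefficient equals the fitted HELP value at zero use minus the control mean. Its variance is

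σ²/61 + (σ²/61) × [1 + 0.5²/(1/12)] = 5σ²/61, against 2σ²/61 without adherence.

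With σ = 6.65, the SE is 6.65 × √(2/61) = 1.20 unadjusted and 6.65 × √(5/61) = 1.90 adjusted (1.92 in simulation).

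**4. Three scenarios**, each with 4,000 simulated trials:

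| Truth | By-arm estimate; rejection | Adherence-adjusted arm estimate; rejection |
| --- | --- | --- |
| (a) Benefit proportional to use: slope −6.8, mean −6.8 × 0.5 = −3.4 | −3.4; 78% | about 0; 5% |
| (b) Same −3.4 benefit whatever the use, use unrelated to prognosis | −3.4; 80% | −3.4; 42% |
| (c) No effect, use correlated 0.3 with better outcome | 0; 5% | about +3.4 (harm); 43% |

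Hand checks:
- (a) At zero use the fitted benefit is −6.8 × 0 = 0.
- (b) 3.4/1.92 = 1.77, and 1.77 − 1.96 = −0.19, a power of about 42%.
- (c) The slope on use is 0.3 × 6.65/√(1/12) = 6.91 in size. Extrapolating from mean use 0.5 to zero gives 6.91 × 0.5 = 3.5, close to the simulated 3.4.

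**5. Sensitivity.** With 10,000 trials per scenario and SD 6.7, use concentrated around the middle (beta 2,2) leaves (a) at 0.00 and takes power in (b) to 31%. A prognosis–outcome correlation of 0.4, with use uniform, takes (c) to +4.5 points with 67.5% false rejection. With that same confounding, a true −3.4 is estimated as +1.1.

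**6. A different specification.** In a repeated measures model with SDQ at 0, 3 and 6 months as the response, the effect on change is the arm-by-time term. A covariate that is constant within a person and entered only as a main effect cancels from within-person contrasts when data are complete and balanced. Mixed-model runs (61 per arm, 30 per scenario) agree:
- (a) −3.36 (SE 1.21) with and without adherence.
- (b) −3.38 (SE 1.19) both ways.
- (c) 0.14 (SE 1.23) both ways.

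The collapse in (a) and the spurious harm in (c) appeared only when adherence was crossed with time or entered as time-varying.

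**The case against.** The strongest reply is step 6. The protocol says repeated measures, not a regression of change, and a plain main effect of adherence does no harm to the arm-by-time term. This stands. A reader might infer that the arm effect necessarily stops measuring the effect of HELP. The document does not support that, because it does not say how adherence enters the model. But it does not exclude the damaging forms either: some repeated measures procedures cross covariates with time by default, and website use is naturally time-varying.

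It can also be said that zero adherence in controls is an inference. That is right: the coding is not stated, and wait-list youth do have use in months 6 to 12. The inference is confined to months 0 to 6, which is the primary window. If adherence were coded missing there instead, controls would drop out of a complete-case model.

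The first research question asks about youth who engage, so adherence is of legitimate interest. Covariate adjustment, however, does not estimate an effect among engagers.

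Two further inferences are tempting and should not be drawn:
- The definition of clinically significant improvement contains "with the reduction occurring only when participants have engaged with the intervention", which may look like the same conditioning. The protocol does not use that definition as an endpoint, analysis set or model term.
- Baseline SDQ is absent from the covariate list, which may look like an omission. In a repeated measures model of change it is already present as the time-0 response.

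**Conclusion.** The point holds in conditional form. The protocol fixes a post-randomisation, self-selected variable as an adjuster of its primary comparison, and controls can have none of it in the primary window. If adherence acts on change, the arm effect becomes a zero-use contrast. In the illustrations a 3.4-point benefit disappears, or power drops to 42% (31% with more concentrated use), or a spurious harm of 3.4 to 4.5 points appears with 43% to 67.5% false rejection. If adherence is a between-person main effect with complete data, the primary contrast is unchanged and nothing is gained. No reading makes the adjustment useful for the primary question.

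The sizes rest on an assumed allocation and sidedness, a back-solved SD, and invented distributions and correlations for use. They show what can happen and are not a forecast of this trial's error.

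**What to change.** Under Efficacy Outcomes, delete intervention adherence from the primary model, and from the between-arm models covered by the closing sentence on all models. State that the primary analysis compares all randomised youth by assigned arm on SDQ change to 6 months, using the 0, 3 and 6-month data and adjusting only for pre-randomisation covariates.

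Report adherence in a separately labelled secondary analysis: a complier-average effect with randomisation as the instrument, or a descriptive dose-response within the HELP arm.

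The cost is wording only, with no new data or visits. The downside is that the engagement analysis becomes secondary.
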